## Abstract

**Background:**

Despite high rates of antenatal care and relatively good access to health facilities, maternal and neonatal mortality remain high in Bangladesh. There is an immediate need for implementation of evidence-based, cost-effective interventions to improve maternal and neonatal health outcomes. The aim of the study is to assess the effect of the intervention namely Group Prenatal Care (GPC) on utilization of standard number of antenatal care, post natal care including skilled birth attendance and institutional deliveries instead of usual care.

**Methods:**

The study is quasi-experimental in design. We aim to recruit 576 pregnant women (288 interventions and 288 comparisons) less than 20 weeks of gestational age. The intervention will be delivered over around 6 months. The outcome measure is the difference in maternal service coverage including ANC and PNC coverage, skilled birth attendance and institutional deliveries between the intervention and comparison group.

**Discussion:**

Findings from the research will contribute to improve maternal and newborn outcome in our existing health system. Findings of the research can be used for planning a new strategy and improving the health outcome for Bangladeshi women. Finally addressing the maternal health goal, this study is able to contribute to strengthening health system.

## Background

There is growing concern about prenatal care for women especially in developing countries, where 80% of the world’s women live [1]. Approximately ninety-nine percent of maternal and neonatal deaths occur in developing countries which is higher in rural areas and among poorer communities [2]. There is an immediate need for implementation of evidence-based, cost-effective interventions to improve maternal and neonatal health outcomes [3]. The Government of Bangladesh is committed to achieving Millennium Development Goal (MDG) 4 and 5; to reduce the under-5 mortality ratio from 146 per 1000 live births in 1990 to 48 per 1000 live births in 2015 and to improve maternal health, by reducing the maternal mortality ratio from 574 to 143 deaths per 100.000 live births by 2015 respectively.

However, the antenatal care (ANC) and postnatal care (PNC) received by medically trained provider is still very low and around 55 and 27% respectively [4]. Although the current practice of the safe motherhood programmes in Bangladesh is to advice pregnant women to deliver their babies in facilities but almost 62% are performed at home (BDHS 2014). Further, though breastfeeding initiation within one hour after birth has increased over time, still it remains below 50% [5]. Despite a fair amount of advocacy around maternal and newborn care, real progress on the ground remains slow [6]. Further efforts are needed to ensure better coverage of antenatal care, as well as improved quality and content of this care [7].

Major causes of maternal death are largely haemorrhage (31%), eclampsia (20%), and abortion (15%) in Bangladesh [5, 7]. Pregnant women are advised to seek care from a medically trained provider or from a facility when they experience complications during pregnancy, at delivery, or postpartum period till 42 days. There are some BCC activities on birth planning and certain danger signs that women may encounter during pregnancy, at delivery, or during postpartum period but the progress is still slow.

The health care that a woman receives during pregnancy, at the time of delivery, and soon after delivery is important for the survival and well-being of both the mother and the child. Prenatal care is a type of preventive care that provides regular check-ups that allow doctors or midwives to treat and prevent potential health problems throughout the course of the pregnancy while promoting healthy lifestyle that benefit both mother and child [8]. Access to prenatal care is critical to achieving the MDGs yet only 55% pregnant woman received prenatal care in Bangladesh in 2009–2013 [4]. In Bangladesh, generally pregnant women receive prenatal care individually by a provider in a private examination room in public, private or NGOs facilities. A previous study found that, traditional individual prenatal care can be supplemented by group prenatal classes, which facilitate support networks, social interaction, and additional education [9]. Group prenatal ideally suited for mothers in developing countries where adverse cultural and traditional practices and low-quality health services interfere with satisfactory implementation of prenatal care [10, 11].

Meeting in a group setting with other women of the same gestational age who are experiencing similar physiological changes of pregnancy nurtures supportive relationships among them are less common in Bangladesh. In the United State, Group prenatal care has been implemented successfully and has had positive impact on perinatal outcomes [12–14]. It provides an integrated approach to prenatal care in a group setting, incorporating family members, peer support, and education. It empowers women by valuing the knowledge and experience that each woman brings to the group, and increases this knowledge through skills building and education. The positive influence of group prenatal care has been strongest for women with low socioeconomic status which not been tried much in a resource poor country like Bangladesh. It is also found that group prenatal care has to positively influence women’s health outcomes after pregnancy and to improve the utilization rate of preventive health services [15]. In Bangladesh, a programme for improving maternal, neonatal and child health in the urban slums named MANOSHI by BRAC also successfully organized group sessions among the women with third trimester of pregnancy for giving health education and encouraging the mother for making a birth plan, safe and hygienic delivery, neonatal and postnatal care [16]. In this project we intend to introduce the GPC in public health facility instead of existing prenatal care. In this Group Prenatal Care (GPC) intervention, prenatal assessment, education and skills development, facilitates learning will be incorporated that will encourage knowledge exchange, and will develop mutual support from its group members which may improve maternal and neonatal outcome.

## Aims and objectives

The overall goal of the project intends to introduce a Group Prenatal Care (GPC) model in selected healthcare facilities in Bangladesh. The specific objective of the study is to assess the effectiveness of GPC in change in coverage of standard number of ANC, PNC, including skilled birth attendance and institutional deliveries; the impact of GPC on maternal and neonatal outcome like preterm birth, caesarean delivery, low birth weight, postpartum complications and breastfeeding rate; and to estimate the incremental cost-outcome ratio of introducing Group Prenatal care in selected facilities. A qualitative study will also be conducted to explore the acceptability and perception of the new GPC model among the intervened mothers.

## Conceptual framework

In group prenatal care, prenatal assessment, education and skills development will be occurred in an atmosphere that facilitates learning, encourages free exchange, and develops mutual support [17]. Group care will permit more time for pregnant women to develop a relationship among each other and to discuss recommended content of care. Peer education approaching (i.e. through peer participation) maternal health promotion will be carried out through peer educators like current pregnant women and experienced mothers. It is expected that group care with peer education will increase interaction with each other of the group members that can encourages women to utilize their knowledge through skill building which may improve their recommended healthcare utilization throughout the pregnancy period. Women thus are better able to take control of their adverse health situation during prenatal and postnatal period Fig. 1.

**Fig. 1 Fig1:**
[figure not shown]
Conceptual framework

## Research design and methods

The study is quasi-experimental in design. The participants who are joining the GPC will be compared with those who receive standard individual prenatal care. Those who are will join the intervention program considered as “intervention group”. On the contrary, ‘comparison group’ are those who do not join this intervention. The intervention group will receive group prenatal care, and the comparison group will receive existing individual prenatal care as provided by the facilities following guidelines recommended by the Ministry of Health and Family Welfare (MOHFW), Government of the People’s Republic of Bangladesh.

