## Randomization

Participants are randomly assigned to the intervention and comparison groups. After meeting the inclusion criterion and obtaining informed consent block randomization is used. Computer-generated random numbers is assigned which have been pre-assigned to one of the two groups (intervention and comparison). The random numbers corresponding to either group has been sealed in an envelope numbered sequentially. The sealed envelope is opened after obtaining the informed consent. Until opening of the envelope, neither the participants nor the healthcare provider is aware of the group that they are assigned to. The envelope that contained “A” meaning “Intervention group” and the envelope contained “B” meaning “Comparison group”.

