## Discussion

A health care system aiming to reduce morbidity and mortality related to pregnancy must focus on maternal and newborn health. The World Health Organization recommended that “Ensuring skilled care for all women during pregnancy, childbirth, and the immediate postnatal period” is one of the strategies to reduce maternal and newborn mortality [23]. Methods described in this study could be a very innovative approach to implement GPC in existing selected facility and expected to have positive perinatal outcomes. Instead of providing usual care based on individual care, this group care at prenatal period will provide good understanding among mothers thus improvement of overall maternal and child health indicators is expected. Group care during pregnancy are proven to be useful in earlier studies that revealed group care ideally suited for mothers in developing countries and positive influence of GPC has been strongest for women with low socio-economic status [11, 12].

This study will compare birth and post partum outcomes for women who participated group prenatal care with women who received individual care. Results will be based on outcomes like increase utilization of prenatal and post natal care, institutional delivery, birth weight etc. Previous studies showed that Group prenatal care had statistically significant beneficial effects on gestational age and birth weight [24] and improve Utilization of postpartum family-planning services [25]. It is now imperative that we intend to experience this GPC approach on to exiting facility.

The study will contribute to improve maternal and newborn outcome in our existing health system. The intervention may improve the health well-being of both mother and child and the family as a whole. If successful, the project will scale up targeting more geographic areas and gradually cover both of the urban and rural areas for understanding the effectiveness of the group prenatal care. Findings of the research can be used for planning a new strategy and improving the health outcome for Bangladeshi women. Finally addressing the maternal health goal, this study is able to contribute to strengthening our health system.

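### The groups are defined by joining GPC in one section and by randomised envelope in another, and the analysis section does not say which definition governs

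*Protocol article*

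**What the plan says.** The protocol article describes the two groups in two ways.

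- **By participation (Research design and methods).** The section states "The study is quasi-experimental in design" and then "The participants who are joining the GPC will be compared with those who receive standard individual prenatal care". It goes on to label the groups: "Those who are will join the intervention program considered as" the intervention group, while the comparison group "are those who do not join this intervention". The Discussion echoes this in looser words: "This study will compare birth and post partum outcomes for women who participated group prenatal care with women who received individual care".
- **By allocation (Randomization).** "Participants are randomly assigned to the intervention and comparison groups". The procedure is specific: "After meeting the inclusion criterion and obtaining informed consent block randomization is used", and "The random numbers corresponding to either group has been sealed in an envelope numbered sequentially". The envelope is opened after consent. Letter A means intervention group and letter B means comparison group.

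The Data analysis section tests differences between the intervention and comparison groups, with regression adjustment for individual socioeconomic factors. It does not say whether a woman's group is her envelope or her participation. The Abstract repeats the quasi-experimental label but does not define the groups by participation.

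**The concern.** The two definitions agree for every woman who does what her envelope says. They part for a woman who draws A and does not join: by the Randomization section she belongs to the intervention group, and by the Research design section she does not.

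This is more than an unstated intention-to-treat principle, which a condensed article may leave to the analysis plan. The article states a rule for group membership that conflicts with its own allocation rule.

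The outcomes make the conflict matter. Antenatal and postnatal coverage, skilled birth attendance and institutional delivery are listed as primary outcomes, and all are forms of care use. A woman who does not take up group care may plausibly also use less care of other kinds. Moving her out of the intervention group would then raise that group's rate and, if she is counted as comparison, lower the other, even if GPC did nothing. Adjustment for socioeconomic factors would not necessarily remove a difference in inclination to seek care. The Study site section reports that 98% of registered pregnant women had a first antenatal visit but only 7% a fourth. That is not a GPC non-joining rate, but it makes full uptake unsafe to assume.

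**Working it through.** **The plan's own figures.** Table 1 gives 227 per group for institutional delivery (28.8%, change of 13 points). The pooled two-proportion formula with two-sided 5% error and 80% power gives 211, and 227 with a continuity correction. The largest row, breastfeeding, gives 250 the same way, and 250 × 1.15 = 287.5, so 288 per group and 576 in total. The figures reproduce and do not depend on how the groups are defined.

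**Inputs for the illustration**
- From the article: institutional delivery p = 0.288 and n = 288 per arm.
- Assumed, because the article gives neither: the share f of the A arm that does not join, and the delivery rate p_n among them.
- Null case: GPC has no effect, so each arm as randomised has rate p.

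**Formulas, with non-joiners counted as comparison**
- Joiners: p_j = (p − f·p_n)/(1 − f), on n(1 − f) women.
- As-joined comparison group: p_c = (p + f·p_n)/(1 + f), on n(1 + f) women.
- Spurious difference: p_j − p_c = 2f(p − p_n)/(1 − f²).
- SE = √[p_j(1 − p_j)/(n(1 − f)) + p_c(1 − p_c)/(n(1 + f))].
- False-positive chance = Φ(z − 1.96) + Φ(−z − 1.96), where z = difference/SE.

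**Worked case, f = 0.20 and p_n = 0.15**
- p_j = (0.288 − 0.030)/0.80 = 0.3225 on 230.4 women.
- p_c = (0.288 + 0.030)/1.20 = 0.2650 on 345.6 women.
- Difference = 0.0575, SE = 0.0389, z = 1.48.
- False-positive chance ≈ Φ(−0.48) ≈ 31.5%.

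| Non-joining f | p_n | Joiners | As-joined comparison | Spurious difference | False-positive chance |
|---|---|---|---|---|---|
| 0% | any | 28.8% | 28.8% | 0 | 5% |
| 10% | 15% | 30.3% | 27.5% | +2.8 points | 11% |
| 20% | 15% | 32.3% | 26.5% | +5.8 points | 31.5% |
| 30% | 15% | 34.7% | 25.6% | +9.1 points | 61% |
| 10% | 20% | 29.8% | 28.0% | +1.8 points | 8% |
| 20% | 20% | 31.0% | 27.3% | +3.7 points | 16% |
| 30% | 20% | 32.6% | 26.8% | +5.8 points | 30% |

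The planned effect on this outcome is 13 points.

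**Two variations, p_n = 15%**
- *Non-joiners dropped instead of moved.* The difference is f(p − p_n)/(1 − f): +1.5, +3.5 and +5.9 points at 10%, 20% and 30%, with false-positive chances of 7%, 14% and 28%.
- *Planned 15% loss.* With 288 × 0.85 ≈ 245 analysed per arm, the differences in the table do not change. The false-positive chances become 10%, 28% and 55%.

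The comparison as randomised has expected difference zero and a 5% false-positive chance in every null case.

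**The case against.** The strongest reply is that the Research design section is a loose overview in imperfect English, and that the operative text is the Randomization section. That section uses the same group names, so the Data analysis section, read with those names, gives a comparison by envelope. The follow-up section tracks all participants, and no section mentions an as-treated or per-protocol analysis. Joining is never tied to a number of sessions and could simply mean being placed in the programme when the envelope is opened. The Discussion sentence is ordinary shorthand for the GPC arm. The rates used above for non-joining and for non-joiners' outcomes are chosen, not reported.

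Much of this stands. A reader might infer that the trial plans an as-treated analysis and discards its randomisation. The article does not support that: it never says how a woman who draws A and does not attend is handled, and the analysis may well follow the envelopes. Nor does it show that women who attend the sessions are the better care seekers. That is plausible, but it is an assumption here, and the bias would reverse sign if non-joiners used more care.

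The reply does not remove the contradiction. The comparison group is expressly defined as women who do not join, the design label points the same way, and nothing shown says that the envelope prevails.

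**Conclusion.** The article contradicts itself on its design label and on who belongs to each group, and leaves open which definition governs the analysis. That much is certain from the text.

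The bias is conditional. It arises only if the participation wording is followed and some women allocated to GPC do not join. It favours GPC only if those women have lower care use. Under the null, for institutional delivery with 288 per arm and non-joiners at an assumed 15% counted as comparison, it runs from about 2.8 points at 10% non-joining to 9.1 points at 30%, with false-positive chances of about 11% to 61%. It shrinks if non-joiners differ less or are dropped, and is zero if all join. These figures show what the wording could allow. They do not predict the trial's result. Because the definition governs every between-group comparison and the remedy is cheap, it should be settled before the groups are analysed.

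**What to change.** - In Research design and methods, and in the matching Discussion sentence, define the intervention group as all women whose envelope was A and the comparison group as all women whose envelope was B.
- State in Data analysis that women are analysed in the group to which they were randomised, regardless of sessions attended.
- Replace the quasi-experimental label, in the Abstract as well, with an individually randomised parallel-group trial.
- Label any contrast of joiners with non-joiners as exploratory.

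The cost is wording. The allocation list already exists, and the planned 288 per group and 576 in total do not change. One consequence should be accepted openly: if some A women do not join, the as-randomised effect is diluted. Assuming non-joiners gain nothing and about 245 women are analysed per arm, a 13-point effect on institutional delivery becomes 13 × 0.9 = 11.7 points at 10% non-joining and 13 × 0.8 = 10.4 points at 20%. Power then falls from about 86% to 78% and 68% (pooled formula without continuity correction). That is the price of an unbiased comparison and is no reason to regroup by participation.

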### Inclusion criteria for participants

Potential participants for either group are to be pregnant women with less than 20 weeks of gestational age, between the age of 18 and 42, without medical complications like pregnancy with jaundice, heart disease, asthma, diabetes, and willing to participate in this study.

### Exclusion criteria for participants

Pregnant women with more than 20 weeks of gestational age and with medical conditions requiring special care are excluded from the study.

### Inclusion criteria for health centers

The health centers will be selected based on two inclusion criteria: at least 10–15 number of clients for ANC visits per day and availability of at least one trained healthcare provider in the facility.

## Sample size

The sample size is estimated using the technique proposed by [18, 19] for comparing two independent proportions. To calculate the sample sizes for detecting difference between intervention and comparison groups, following formula has been employed$$ \mathrm{n}=\frac{{\left[\ {\mathrm{Z}}_{\upalpha}\sqrt{\left(\mathrm{r}+1\right)\overline{\mathrm{P}}\overline{\mathrm{Q}}}+{\mathrm{Z}}_{\upbeta}\sqrt{\Big({\mathrm{r}\mathrm{P}}_1{\mathrm{Q}}_1+{\overline{\mathrm{P}}}_2{\overline{\mathrm{Q}}}_2}\ \right]}^2}{{\mathrm{r}\updelta}^2} $$

Where,

a) $$ \updelta =\left|{\mathrm{P}}_2-{\mathrm{P}}_1\right| $$, b) $$ \overline{\mathrm{P}}=\frac{{\mathrm{P}}_1+\mathrm{r}{\mathrm{P}}_2}{\mathrm{r}+1} $$, c) $$ \overline{\;\mathrm{Q}}=1-\overline{\mathrm{P}} $$

d) α, the probability of type I error,e) β, the probability of type II error, or (1-power of the test)

f) P_1_, proportion of characteristic present in intervention group, g) P_2_, proportion of characteristic present in comparison group d) r, ratio of required sample size from two groups (*r* = 1 in this study)

It is expected that due to intervention different types of indicators (Table 1) will change. Using this percentage of expected change difference in intervention and comparison groups at 5% error level and 80% power the estimated sample size for each group is reported in following table. The highest sample size (250) is estimated for breastfeeding rate. Considering the 15% lost to follow-up, the sample size is 288 for each group. Therefore, in total 576 pregnant women (288 cases and 288 comparisons) will be enrolled randomly in this study. Recruitment will take place from May 20, 2015 to May 30, 2016 and intervention was completed on October 30, 2016. Data collection is ongoing now among the enrollees.

**Table 1 Tab1:** Sample size estimation

Indicators	Parentage	% of expected change	Required sample size	Sample size (15% lost to follow-up rate)	Total sample
ANC^1^	55.0%	14%	202	232	464
PNC^1^	27.0%	15%	170	196	392
Skilled-birth attendance^1^	31.7%	16%	158	182	364
Institutional deliveries^1^	28.8%	13%	227	261	522
Preterm birth^2^	22.30%	−12%	164	189	378
Low birth weight^3^	36%	−12%	245	282	564
Postpartum complications	36%	−13%	208	239	478
Breastfeeding rate (2–3 m)^1^	71.0%	11%	250	288	576

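### The 15% loss is added as n × 1.15 rather than n/0.85, and, separately, the printed formula omits the continuity correction behind Table 1; only breastfeeding is affected, by under one point of power

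*Protocol article*

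**What the plan says.** The Sample size section of the protocol article displays a formula for comparing two independent proportions and says that "for detecting difference between intervention and comparison groups, following formula has been employed". The settings are given as "at 5% error level and 80% power", with equal groups. The text does not say whether the 5% is one-sided or two-sided, and it mentions no continuity correction.

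Table 1 then lists a required size per group for eight indicators, a second column that allows for 15% loss, and a total. One row sets the size of the trial: "The highest sample size (250) is estimated for breastfeeding rate". Its entries read "71.0% 11% 250 288 576", that is, 71% with an 11-point rise, 250 required, 288 after the loss allowance and 576 in total. The text carries this forward as "Considering the 15% lost to follow-up, the sample size is 288 for each group".

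**The concern.** Multiplying by 1.15 adds 15% of the required number. A loss rate removes 15% of the enrolled number, which is larger, so the multiplication always falls a little short. Breastfeeding is the row where this counts: it fixes 288, so no larger requirement is there to absorb the gap. It is also one of the outcomes listed under Primary outcome.

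The second matter is reproducibility. The article prints a formula, says it was used, and prints results that it does not give. A reader who checks any row of Table 1 gets a different required size. At stake are whether the stated 80% power survives the stated 15% loss, and whether the basis for the sample size can be checked at all.

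**Working it through.** **Inputs, all from the Sample size section and Table 1.** α = 0.05, power 80%, r = 1, and for each indicator the baseline percentage and the expected change, read as percentage points. Two-sided testing is my assumption, since sidedness is not stated. It is the reading that fits: for breastfeeding, one-sided testing gives 183, or 201 with a continuity correction. Reading the change as relative gives 483.

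**Printed formula, breastfeeding (0.71 v 0.82, δ = 0.11).** The mean proportion is 0.765.

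- 1.960 × √(2 × 0.765 × 0.235) = 1.1752
- 0.842 × √(0.82 × 0.18 + 0.71 × 0.29) = 0.842 × √0.3535 = 0.5004
- m = (1.1752 + 0.5004)² / 0.0121 = 232.0

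Taking the bars over P2 and Q2 in the second root literally, as the pooled mean, gives about 227. Neither reading is 250.

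**With a continuity correction.** n = (m/4) × [1 + √(1 + 4/(mδ))]² = (232.0/4) × [1 + √(1 + 4/25.5)]² = 249.9, rounded up to 250. This is the plan's figure.

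**Loss step.** 250 × 1.15 = 287.5, printed as 288. The requirement under 15% loss is 250/0.85 = 294.1, so 295 per group and 590 in total: 7 more per group, 14 more overall. With 288 enrolled, 288 × 0.85 = 244.8 remain, about 5 below 250. The loss that 288 can bear is 1 − 250/288 = 13.2%.

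**Power for breastfeeding at 244.8 per group.**

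- Uncorrected: Φ[(0.11 × √244.8 − 1.1752)/√0.3535] = Φ(0.918) = 82.1%
- Corrected: replace 244.8 by 244.8 − 2/0.11 + 1/(244.8 × 0.11²) = 226.96, which gives Φ(0.811) = 79.1%

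**All rows by the same steps.** The last two columns give power at 244.8 per group, that is, 288 enrolled less 15%.

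| Indicator | Printed formula | With correction | Table 1 n | n × 1.15 | Table 1 with loss | n/0.85, rounded up | Power, corrected | Power, uncorrected |
|---|---|---|---|---|---|---|---|---|
| ANC | 187.5 | 201.5 | 202 | 232.3 | 232 | 238 | 87% | 89% |
| PNC | 156.5 | 169.5 | 170 | 195.5 | 196 | 200 | 93% | 94% |
| Skilled attendance | 145.6 | 157.9 | 158 | 181.7 | 182 | 186 | 94% | 95% |
| Institutional delivery | 211.0 | 226.1 | 227 | 261.05 | 261 | 268 | 83% | 86% |
| Preterm birth | 147.5 | 163.8 | 164 | 188.6 | 189 | 193 | 94% | 95% |
| Low birth weight | 227.7 | 244.1 | 245 | 281.75 | 282 | 289 | 80.1% | 82.8% |
| Postpartum complications | 192.0 | 207.1 | 208 | 239.2 | 239 | 245 | 87% | 89% |
| Breastfeeding | 232.0 | 249.9 | 250 | 287.5 | 288 | 295 | 79.1% | 82.1% |

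The corrected version, rounded up, matches Table 1 in eight rows of eight; the printed formula matches in none. The loss column is n × 1.15, rounded, in all eight.

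**The case against.** The best defence is that the study is adequately powered by the formula it prints. That formula needs 233 evaluable women for breastfeeding, and 233/0.85 = 274.1, so 275 per group, which is below 288. The Data analysis section plans a t-test for proportions and regression and names no continuity-corrected test, so 82.1% is arguably nearer to the planned analysis than 79.1%. This stands. It means that the missing correction does not add to the shortfall; it works against it.

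It can also be said that the formula comes from two cited sources that may contain the correction, and that a condensed article may have dropped it from the display. That would explain the mismatch, and it agrees with the finding that 250 is not a miscalculation. It does not remove the mismatch, because the article presents the displayed formula as the one employed and prints its supposed results beside it.

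Finally, the 15% is itself a planning figure, the deficit is about 5 evaluable women per group, and the expected changes of 11 to 16 points are less certain than that. This is a fair argument about size, and it is why the point is rated minor. It is no reason to leave the arithmetic as printed.

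**Conclusion.** The concern holds as two separate errors of small effect.

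- **Loss allowance.** It is calculated wrongly in every row. Measured against the plan's own 250, enrolment of 288 falls short by 7 per group at the stated 15% loss, and power for breastfeeding drops from 80% to 79.1% on the corrected basis.
- **Formula.** The one displayed is not the one that produced Table 1. This is a reporting error; the tabulated sizes are sound for the corrected method.

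A reader might infer three stronger things that the document does not support. One is that the trial is underpowered overall: six of the other seven tabulated indicators have clear room at 244.8 per group, including all four coverage outcomes in the stated aim. Another is that the two errors compound: they offset, and by the printed formula power stays at 82.1%. The third is that low birth weight also falls short, because 245/0.85 = 288.2 rounds up to 289. That comes from dividing a number already rounded up. From the unrounded 244.13, the requirement is 244.13/0.85 = 287.2, so 288 is enough and power is 80.1%.

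The conclusion rests on a two-sided 5% level, changes in percentage points, and 15% meaning a share of the women enrolled. Severity: minor.

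**What to change.** Make three corrections to the Sample size section.

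1. Display the continuity-corrected formula that was used, and state that the test is two-sided.
2. Recalculate the loss column of Table 1 as n/0.85. From the printed n, the rows become 238, 200, 186, 268, 193, 289, 245 and 295, and the totals double accordingly. Add a note that the unrounded low birth weight requirement is met by 288.
3. Keep enrolment at 288 per group and restate what it provides for breastfeeding: about 79% power with the continuity correction (82% without) at 15% loss, or 80% if loss does not exceed about 13%.

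The cost is one formula, one table column with its totals, and one sentence. The section gives recruitment as ending on May 30, 2016 and the intervention as complete, so no added recruitment is proposed. The stated power for one indicator falls by about one point.
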